### Outcomes

2.4

The outcome measures of the TeleRiab4FRA study were defined to provide a multidimensional evaluation of the effects of high-technology telerehabilitation in frail and pre-frail older adults with CHF. Outcomes include functional capacity, frailty status, physical performance, health-related quality of life, cognitive function, biochemical parameters, caregiver-related outcomes, technological usability, treatment adherence, and safety. All outcomes will be collected according to the pre-specified assessment schedule and in line with the registered trial protocol.

The primary outcome is the change in functional capacity from baseline to the end of the 8-week intervention, measured as VO₂peak during CPET (35, 36). The primary efficacy analysis will compare VO₂peak at 8 weeks between the telerehabilitation group and the control group, adjusted for baseline values. VO₂peak will also be assessed at the 24-week follow-up to evaluate the maintenance of treatment effects over time (37).

The key secondary outcome is the change in frailty status assessed using the IFI (26), which will be collected at baseline, 4 weeks, 8 weeks, 16 weeks, and 24 weeks, and changes over time will be compared between the telerehabilitation and control groups.

Physical performance will be assessed using the SPPB, which includes balance, gait speed, and chair stand tests (38, 39). The SPPB provides a composite score ranging from 0 to 12, with higher scores indicating better lower-extremity function and physical performance. SPPB will be assessed at baseline, 4 weeks, 8 weeks, 16 weeks, and 24 weeks.

Health-related quality of life will be evaluated using the Short Form-36 Health Survey (SF-36), which assesses multiple domains, including physical functioning, role limitations, bodily pain, general health, vitality, social functioning, emotional well-being, and mental health (40, 41). Scores range from 0 to 100, with higher scores indicating better perceived health status and quality of life. SF-36 will be administered at baseline, 8 weeks, and 24 weeks.

Cognitive function will be evaluated using both the Mini-Mental State Examination (MMSE) (42) and the Montreal Cognitive Assessment (MoCA) (43). The MMSE assesses global cognitive function, including orientation, attention, memory, language, and visuospatial abilities, with total scores ranging from 0 to 30 and higher scores indicating better cognitive performance (44). The MoCA will be used to provide an additional assessment of cognitive domains relevant to executive function, attention, memory, and self-management (45). Both MMSE and MoCA will be collected at baseline, 4 weeks, 8 weeks, 16 weeks, and 24 weeks.

Biochemical parameters will include B-type natriuretic peptide (BNP) and atrial natriuretic peptide (ANP), expressed in picograms per milliliter (46). Changes in BNP and ANP levels will be assessed at baseline, 8 weeks, and 24 weeks to explore potential biological changes associated with the rehabilitation program and HF status.

Caregiver-related outcomes will include caregiver burden and perceived stress. Caregiver burden will be assessed using the 12-item Zarit Burden Interview (ZBI-12) (47), while perceived stress will be assessed using the 10-item Perceived Stress Scale (PSS-10) (48). Both instruments will be administered at baseline and at 8 weeks to explore the impact of the rehabilitation pathway on caregivers.

Technological usability and acceptability will be evaluated only in the telerehabilitation group using the System Usability Scale (SUS) (49), a 10-item questionnaire with total scores ranging from 0 to 100, where higher scores indicate better perceived usability. SUS will be administered at the end of the 8-week intervention.

Treatment adherence will be assessed as the percentage of scheduled motor and cognitive training sessions completed during the 8-week intervention period. In the telerehabilitation group, adherence and fidelity will be documented through platform-based session records, attendance, therapist records, and available sensor-derived performance data. In the control group, adherence and fidelity will be assessed through daily activity diaries, caregiver competency verification, structured weekly contacts, and review of whether the prescribed frequency, duration, and exercise content were followed. Major deviations and reasons for missed or modified sessions will be recorded in the CRF.

Safety outcomes will include adverse events, symptoms occurring during exercise, abnormal clinical parameters, technical issues affecting session delivery, and any interruption or modification of the rehabilitation program. Safety information will be collected throughout the intervention and follow-up period (Table 4).

**Table 4 T4:** TeleRiab4FRA outcome measures by assessment timepoint. ANP, atrial natriuretic peptide; BNP, B-type natriuretic peptide; IFI, Italian Frailty Index; MMSE, Mini-Mental State Examination; MoCA, Montreal Cognitive Assessment; PSS-10, 10-item Perceived Stress Scale; SF-36, Short Form-36 Health Survey; SPPB, Short Physical Performance Battery; SUS, System Usability Scale; VO₂peak, peak oxygen uptake; ZBI-12, 12-item Zarit Burden Interview.

Outcome type	Outcome measure	Domain	Baseline	4 weeks	8 weeks	16 weeks	24 weeks
Primary	Change in VO₂peak	Functional capacity	✓		✓		✓
Secondary, key	Change in IFI	Frailty status	✓	✓	✓	✓	✓
Secondary	Change SPPB score	Physical performance	✓	✓	✓	✓	✓
Secondary	Change in SF-36 score	Quality of life	✓		✓		✓
Secondary	Change in MMSE score	Cognitive function	✓	✓	✓	✓	✓
Secondary	Change in MoCA score	Cognitive function	✓	✓	✓	✓	✓
Secondary	Change in BNP levels	Biochemical	✓		✓		✓
Secondary	Change in ANP levels	Biochemical	✓		✓		✓
Secondary	Change in ZBI-12 score	Caregiver burden	✓		✓		
Secondary	Change in PSS-10 score	Caregiver stress	✓		✓		
Secondary	SUS score	Usability and acceptability			✓		
Secondary	Treatment adherence	Process measure		✓	✓		
Safety	Adverse events	Safety and feasibility		✓	✓	✓	✓

SUS will be administered only to participants allocated to the telerehabilitation group. Treatment adherence will be assessed throughout the 8-week intervention period as the percentage of scheduled motor and cognitive training sessions completed. The 24-week assessment of VO₂peak will be used to evaluate maintenance of treatment effects over time and will not replace the primary post-treatment analysis at 8 weeks.

### Safety management and contingency planning

2.5

A structured safety management and contingency plan will be implemented to minimize clinical and operational risks during the TeleRiab4FRA study. The safety procedures will apply to both study groups, with specific measures adapted to the mode of delivery of each intervention.

In the telerehabilitation group, all sessions will be delivered synchronously and remotely supervised by qualified healthcare professionals. During each session, the rehabilitation team will monitor the patient's clinical status, exercise execution, and physiological response to training. The telerehabilitation platform will support remote monitoring of relevant clinical parameters, including heart rate, peripheral oxygen saturation, blood pressure, and single-lead electrocardiographic data. These data will be used to guide exercise progression, verify tolerance, and identify potential warning signs.

Before starting the home-based program, patients and caregivers will receive in-person training on the use of the telerehabilitation devices, correct sensor placement, recognition of warning symptoms, and procedures to follow in case of clinical or technical problems. Patients will be instructed to stop exercise and immediately inform the rehabilitation team in case of chest pain, marked dyspnea, dizziness, palpitations, excessive fatigue, neurological symptoms, altered consciousness, falls, or any other concerning symptom.

The rehabilitation session will be interrupted in the presence of abnormal clinical parameters, relevant symptoms, unsafe exercise execution, or technical issues that prevent adequate supervision. In such cases, the patient will be contacted by the rehabilitation team and, when necessary, referred for cardiological evaluation, in-person rehabilitation assessment, or emergency medical care according to local clinical procedures.

In the control group, patients will perform the home-based program under the supervision of a caregiver or family member. Caregivers will receive specific instructions on how to support the patient during the sessions, recognize signs of intolerance, measure basic clinical parameters when required, interrupt exercise in case of warning symptoms, and contact the clinical team if clinical concerns arise. The daily activity diary will also be used to record session completion, perceived tolerance, symptoms, and any adverse events.

Technical contingency procedures will be applied in the telerehabilitation group. In case of device malfunction, connectivity problems, difficulties in using the platform, or inadequate data transmission, remote technical assistance will be provided. If the problem cannot be resolved and safe remote supervision cannot be ensured, the session will be postponed, modified, or replaced by an in-person assessment or session, according to clinical judgement and organizational feasibility.

All adverse events, symptoms occurring during exercise, abnormal parameters, technical issues, protocol deviations, and interruptions of the rehabilitation program will be documented in the CRF. Serious adverse events will be managed and reported according to Good Clinical Practice principles, local institutional procedures, and applicable regulatory requirements. This safety framework is intended to ensure patient protection, therapeutic continuity, and traceability of clinical and technical events throughout the study (Figure 2).

**Figure 2 F2:**
[figure not shown]
Safety thresholds and actions. BP, blood pressure; ECG, electrocardiogram; HR, heart rate; SBP, systolic blood pressure; SpO₂, peripheral oxygen saturation.

### Statistical analysis

2.6

All statistical analyses will be performed according to a pre-specified Statistical Analysis Plan before database lock. Descriptive statistics will be used to summarize baseline demographic, clinical, functional, cognitive, biochemical, and caregiver-related characteristics. Continuous variables will be reported as mean and standard deviation or median and interquartile range, according to data distribution. Categorical variables will be summarized as absolute frequencies and percentages. Normality will be assessed using graphical methods and appropriate statistical tests.

The primary analysis will be conducted according to the intention-to-treat (ITT) principle, including all randomized participants and analyzing them according to their original allocation group. A per-protocol (PP) analysis will also be performed as a sensitivity analysis, including participants who complete at least 80% of the scheduled motor and cognitive training sessions without major protocol deviations. The safety population will include all participants who start the assigned rehabilitation program and will be used for the description of adverse events and safety-related outcomes.

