#### Telerehabilitation group

2.2.1

Participants allocated to the telerehabilitation group will receive an 8-week synchronous high-technology telerehabilitation program delivered through a CE-marked digital platform. The intervention will combine sensorimotor and cognitive training and will be remotely supervised by qualified healthcare professionals. Before starting the home-based telerehabilitation program, patients and caregivers will receive in-person training on the use of the platform and devices, together with technical instructions and safety procedures.

The telerehabilitation system will allow real-time audio-video interaction between the patient and the rehabilitation team, remote supervision of exercise execution, and monitoring of relevant clinical parameters, including electrocardiographic tracing, heart rate, peripheral oxygen saturation, and blood pressure. Remote monitoring will be used to support safety during the sessions, guide exercise progression, and identify any clinical or technical issue requiring intervention. In case of abnormal clinical parameters, symptoms, or difficulties in performing the exercises, the session may be interrupted and the patient may be referred for additional clinical evaluation.

The motor training program will last approximately 60 min per session, including warm-up, active training, and cool-down. Exercise intensity will be individualized according to baseline CPET findings, with a target progressing toward approximately 70% of baseline VO₂peak; when CPET-based prescription is not feasible, 75%–80% of the maximum heart rate recorded during ergometric testing will be used. The prescription will be progressively adapted to exercise tolerance, clinical status, and frailty level. The cognitive training component will last approximately 30 min per session and will include exercises targeting memory, visuospatial abilities, executive functions, and psychomotor speed.

Training load, task complexity, and exercise duration may be increased when the participant completes the prescribed activities with correct execution, acceptable perceived exertion, stable symptoms, and physiological values within the study safety thresholds. The load will be maintained, reduced, or the session interrupted in the presence of excessive Borg-rated exertion, relevant symptoms, abnormal vital signs, unsafe movement execution, or incomplete recovery. All adaptations and their reasons will be recorded by the treating professional.

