#### Primary endpoint analysis

2.6.1

The primary endpoint is the change in functional capacity from baseline to the end of the 8-week intervention, assessed by VO₂peak measured during cardiopulmonary exercise testing.

The primary efficacy analysis will compare VO₂peak at 8 weeks between the telerehabilitation group and the control group using analysis of covariance (ANCOVA), with treatment group as the fixed factor and baseline VO₂peak as the mandatory covariate. Additional pre-specified covariates may include age, sex, NYHA class, and baseline frailty level, if clinically relevant or imbalanced between groups at baseline. The treatment effect will be expressed as adjusted mean difference between groups, with 95% confidence interval and *p*-value.

As a supportive analysis, the absolute change in VO₂peak from baseline to 8 weeks will also be calculated and compared between groups. A longitudinal analysis will be performed using a linear mixed model for repeated measures, including time, group, and group-by-time interaction as fixed effects and participant as a random effect. This model will allow the evaluation of VO₂peak trajectories over time, including baseline, post-treatment, and follow-up assessments. The 24-week assessment will be used to evaluate the maintenance of treatment effects and will be interpreted as a follow-up analysis rather than as the primary confirmatory endpoint.

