#### Sample size calculation

2.6.3

The sample size was calculated on the basis of the primary endpoint, defined as the change in functional capacity measured by VO₂peak during cardiopulmonary exercise testing from baseline to the end of the 8-week intervention.

A between-group difference of 2.5 mL/kg/min in VO₂peak (50) was considered clinically meaningful. Assuming a standard deviation of 3.5 mL/kg/min, corresponding to a Cohen's d effect size of approximately 0.71, the sample size calculation was performed using G*Power software, based on a two-tailed test for the difference between two independent means, with a significance level of *α* = 0.05, statistical power of 80%, and 1:1 allocation.

The calculation indicated that 33 participants per group, corresponding to 66 participants overall, are required to detect the expected difference in the primary endpoint. Considering an anticipated dropout rate of approximately 15%–20%, the study plans to enroll approximately 80 participants overall, in order to preserve adequate statistical power for the primary efficacy analysis.

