#### Handling of missing data and dropouts

2.6.4

Missing data will be described by treatment group, outcome, and assessment timepoint. The amount, pattern, and potential reasons for missingness will be examined to evaluate whether missing data are likely to be missing completely at random, missing at random, or not missing at random.

The primary analysis will be conducted on the ITT population. Linear mixed models for repeated measures will be used as part of the analytical strategy because they allow inclusion of participants with partially observed follow-up data under the missing at random assumption. If the proportion of missing data at the primary post-treatment assessment is relevant or unbalanced between groups, sensitivity analyses using multiple imputation will be performed. The imputation model may include treatment group, baseline value of the outcome, age, sex, NYHA class, frailty level, and other variables associated with missingness or outcome values.

Dropouts and protocol deviations will be documented in the CRF, including the timing and reason for withdrawal whenever available. Participants who discontinue the intervention but remain available for outcome assessment will be invited to complete follow-up evaluations according to the original study schedule. Per-protocol analyses will be conducted as sensitivity analyses to assess the robustness of the primary findings among participants with adequate intervention exposure and without major protocol deviations.

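### The primary analysis is described as including all randomised participants, but the named model can use only those with both a baseline and a week-8 VO₂peak, and the planned remedies do not close the gap

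*Protocol article*

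**What the plan says.** Four statements in the protocol article bear on this.

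- **Population (section 2.6).** The primary analysis follows the "intention-to-treat (ITT) principle, including all randomized participants and analyzing them according to their original allocation group".
- **Model (section 2.6.1).** "The primary efficacy analysis will compare VO₂peak at 8 weeks between the telerehabilitation group and the control group using analysis of covariance (ANCOVA"). The same sentence goes on to fix the terms of that model: "with treatment group as the fixed factor and baseline VO₂peak as the mandatory covariate". Nothing is said about a participant without a week-8 value. A comparison of change scores follows as supportive, and then: "A longitudinal analysis will be performed using a linear mixed model for repeated measures".
- **Expected loss (section 2.6.3).** The calculation requires 66 participants. "Considering an anticipated dropout rate of approximately 15%–20" per cent, it enrols about 80.
- **Missing data (section 2.6.4).** ITT is restated. Mixed models are given as one element of the strategy, valid under missing at random (MAR). If missingness at week 8 "is relevant or unbalanced between groups, sensitivity analyses using multiple imputation will be performed". No threshold is attached to either term. Participants who stop the intervention are invited to remaining assessments.

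Table 4 schedules VO₂peak at baseline, 8 weeks and 24 weeks only. SPPB and IFI are also collected at weeks 4 and 16.

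**The concern.** An ANCOVA without imputation silently omits anyone lacking the outcome or the covariate. The half of the ITT promise about analysing by original allocation is kept; the half about including everyone randomised is not. A SAP written to this text inherits the conflict.

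This matters because loss in this trial could well be related to outcome and could differ between arms. Section 5 accepts that retention may depend on digital literacy, connectivity and caregiver availability. Section 2.5 describes device and connection failures that only the telerehabilitation arm can experience. Clinical instability and poor exercise tolerance plausibly affect both attendance and VO₂peak. A comparison among completers then answers a different question from the one stated. The decision whether to impute would be taken after the extent and balance of missingness are known, by a criterion that nobody has fixed.

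**Working it through.** **1. The plan's own sample size.** Inputs from section 2.6.3: difference 2.5, SD 3.5, two-sided α = 0.05, power 80%, 1:1. With d rounded to 0.71, the two-sample t-test (noncentral t) needs 33 per group, power 0.811; the stated figure is reproduced. Inflation: 66/(1 − 0.15) = 77.6, so 78; 66/(1 − 0.20) = 82.5, so 83. About 80 lies in that range. The calculation therefore already treats dropouts as not contributing to the primary comparison.

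**2. How many could be left out.** 80 × 0.15 = 12 and 80 × 0.20 = 16, leaving 68 or 64. Power with d = 2.5/3.5 is 0.827 at 68 and 0.803 at 64, against 0.884 if all 80 were observed. Power is not the problem; what is estimated, and its possible bias, is.

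**3. What the mixed model adds.** VO₂peak has two post-baseline times, weeks 8 and 24. A participant lost before week 8 for good supplies a baseline value and nothing else. One who misses week 8 but attends week 24 does contribute follow-up data.

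**4. Size of bias (illustrative).** Let D be the mean shortfall in week-8 VO₂peak, given baseline, of those missing compared with those observed in the same arm, and m the share missing. The completer contrast is off by D_tele × m_tele − D_ctrl × m_ctrl. D of 1.5 to 2.5 mL/kg/min and the splits below are assumptions.

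| Scenario | D = 1.5 | D = 2.5 |
|---|---|---|
| Same D in both arms, 20% vs 10% missing | 1.5 × 0.10 = 0.15 | 2.5 × 0.10 = 0.25 |
| Shortfall in telerehabilitation only, 15% missing | 1.5 × 0.15 = 0.225 | 2.5 × 0.15 = 0.375 |
| Shortfall in telerehabilitation only, 20% missing | 1.5 × 0.20 = 0.30 | 2.5 × 0.20 = 0.50 |

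The range is 0.15 to 0.50 mL/kg/min, that is 0.15/2.5 = 6% to 0.50/2.5 = 20% of the target difference. As set out, the bias favours telerehabilitation; with heavier loss in the control arm the first row changes sign.

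**5. Effect on type I error (illustrative).** A simulation with no true effect used 40 per arm, an assumed baseline to week-8 correlation of 0.7, and 4,000 runs per setting. With random loss in both arms, the completer ANCOVA rejected in about 5% of runs. With random loss in control but loss related to poor response in telerehabilitation, bias was about +0.44 (15% loss) to +0.56 (20% loss) mL/kg/min, and the rejection rate about 0.13 to 0.16.

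**The case against.** The case for leaving the plan largely as it is has real substance, and it rules out several stronger readings.

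- **A reader might infer that no MAR analysis is guaranteed.** That is not so. Only imputation is conditional; sections 2.6.1 and 2.6.4 commit to the mixed model without condition. It is, however, not the primary analysis.
- **A reader might infer that differential loss would go unaddressed.** Imbalance between arms is one of the two named triggers. What is missing is any definition of either.
- **A reader might take 12 to 16 as the number that will be missing.** It is a planning figure. Those who stop treatment are invited to follow-up, so some dropouts may still have a week-8 test.
- **A reader might infer that week-4 measures are barred from the imputation model.** The list in section 2.6.4 is permissive and admits other variables related to outcome or missingness.
- **A reader might infer from "when CPET-based prescription is not feasible" in section 2.2.1 that participants without a baseline VO₂peak are randomised.** That phrase concerns how exercise is prescribed. Section 2.1 randomises after the baseline assessment is complete, and Table 4 includes VO₂peak in it. The documents do not support a new eligibility criterion.

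The strongest statistical objection is that, if missingness depends only on arm and baseline VO₂peak, the completer ANCOVA with the correct mean model is already consistent. This stands. It means that MAR imputation helps only as far as auxiliary data, such as week-4 SPPB and IFI or week-24 VO₂peak, explain the loss. The remaining risk calls for an analysis that departs from MAR. None of this reconciles the description of the population with the model.

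**Conclusion.** The concern holds as a conflict between sections 2.6, 2.6.1 and 2.6.4: the population is everyone randomised, the primary model cannot include everyone, and no stated remedy makes it do so. The mixed model is secondary and nearly uninformative for early leavers. Imputation is conditional on an undefined judgement made after the data are seen. No planned analysis departs from MAR, although section 2.6.4 recognises that data may be missing not at random; the per-protocol analysis restricts the set further and cannot test this.

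At the planned dropout rate, up to about 12 to 16 of 80 are affected. The possible bias of 0.15 to 0.50 mL/kg/min rests on assumed deficits and arm-specific patterns, not on anything in the protocol, and could be nil if loss is unrelated to outcome given arm and baseline. The sample size is sound. Because the primary comparison is affected and the remedy is cheap, the conflict should be resolved before database lock.

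**What to change.** Reconcile sections 2.6, 2.6.1 and 2.6.4 by naming one primary estimator that covers all randomised participants. For example:

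1. Impute missing week-8 VO₂peak separately by arm in every case, using baseline VO₂peak, the stratification factors (frailty status, NYHA class), age, sex, week-4 SPPB and IFI, and week-24 VO₂peak. Fit the specified ANCOVA to each completed dataset and combine by Rubin's rules.
2. Delete the condition that makes imputation depend on missingness being relevant or unbalanced.
3. Keep the observed-case ANCOVA as a supportive analysis.
4. Add one delta-adjusted (tipping-point) sensitivity analysis that progressively worsens the imputed values in the telerehabilitation arm.

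If the sponsor prefers to keep the observed-case ANCOVA as primary, describe its set as randomised participants with baseline and week-8 VO₂peak, and run the imputation and the delta-adjusted analysis unconditionally.

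The cost is protocol and SAP wording and some programming. Eligibility, assessments and sample size need no change.
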